### 2.11. Statistical Analysis

An intention-to-treat (ITT) analysis will be used for data analysis, as specified by CONSORT guidelines [26]. Statistical analysis will be performed using IBM SPSS Statistics version 25. Descriptive analysis will be used to analyse the demographic data in each participant group. The Shapiro–Wilk test will be used to assess the normality, and the data will be presented as mean ± standard deviation. In contrast, skewed data will be reported in the median and interquartile range. The categorical data will be expressed as a proportion (percentages). Comparisons of demographic and clinical characteristics at the baseline of both the study groups will be tested by independent sample *t*-tests and the chi-square or nonparametric Mann–Whitney *U*-test, respectively.

Repeated-measures analysis of variance (ANOVA) will be used to analyse the primary and second outcomes with regard to time (baseline, 3-month, and 6-month follow-up) as the within-group factor and interventions (standard telerehabilitation versus coaching-based teleoccupational guidance) as the between-group factor. We will evaluate the main effects of time, group, and time-group interaction effects. The Mauchly test will be performed to check the sphericity of the data; if significant, the Greenhouse–Geisser statistic will be used to adjust the degrees of freedom [27]. The level of significance will be set at 0.05.

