### 2.10. Sample Size

The RNLI, commonly used as a reliable outcome measure in occupational therapy research, will be employed for sample-size estimation. According to our preliminary test and previous studies, the minimum significant difference between the 2 groups in the T2–T1 interval for the RNLI in the survey is 14 points [25]. The standard deviation of the measure was reported as 21 points in previous studies [25]. Setting the *α* at 0.05 (two-tailed) and the power at 80% and assuming a drop-out rate of 20%, the minimum sample size for each arm is 46. Based on this estimation, we will recruit at least 92 participant dyads (92 participants and 92 caregivers in each group–intervention versus standard telerehabilitation) for the study.

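### The repeated-measures ANOVA named for the primary outcome, run as written, drops every participant with a missed visit and so does not match the promised intention-to-treat analysis

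*Protocol article*

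**What the plan says.** Section 2.11 sets the analysis principle: "An intention-to-treat (ITT) analysis will be used for data analysis, as specified by CONSORT guidelines [26". The same section fixes the method: "Repeated-measures analysis of variance (ANOVA) will be used to analyse the primary and second outcomes with regard to time". The within-subject factor has three levels: "time (baseline, 3-month, and 6-month follow-up) as the within-group factor". The form of the ANOVA is also given: "The Mauchly test will be performed to check the sphericity of the data; if significant, the Greenhouse–Geisser statistic will be used". The software is stated: "Statistical analysis will be performed using IBM SPSS Statistics version 25".

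Section 2.10 plans for loss: "assuming a drop-out rate of 20%, the minimum sample size for each arm is 46". The target difference is on a change score: "the minimum significant difference between the 2 groups in the T2–T1 interval for the RNLI in the survey is 14 points", with a standard deviation of 21 points.

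Elsewhere, section 2.15 speaks only of preventing drop-out, and the Discussion says only that drop-outs will be counted and their reasons examined. The article names no imputation, mixed model or other rule that keeps a participant with a missed visit in the analysis.

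**The concern.** Mauchly's test and the Greenhouse–Geisser correction identify the classical repeated-measures ANOVA, not a likelihood-based mixed model. The classical procedure works on participants with a value at every level of the time factor and deletes the rest listwise. A survivor with baseline and 3-month RNLI who misses month 6 is therefore removed from the 3-month comparison as well, although the data for it exist.

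What is at stake is the population being compared. Survivors, caregivers and therapists are unblinded (section 2.4) and the RNLI is self-reported (section 2.8.1), so it is plausible that staying in the trial depends on perceived benefit, and differently in the two arms. The completers would then no longer be comparable by randomisation, and the result would carry an intention-to-treat label that the method does not support.

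**Working it through.** **Inputs from the article.** Difference 14, SD 21, two-sided alpha 0.05, power 80%, drop-out 20%, 46 per arm (section 2.10); 1:1 allocation (section 2.4); three visits (section 2.11).

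**Step 1: reproduce the sample size.**
- Normal approximation: n = 2 × [21 × (1.960 + 0.842) / 14]² = 35.3, so 36 per arm; 36 / 0.8 = 45.
- Two-sample t-test: n = 36.3 per arm; 36.3 / 0.8 = 45.4, so 46. Rounding to 37 first gives 37 / 0.8 = 46.25, so 47.

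The stated 46 reproduces. It rests on about 36 to 37 analysed per arm, so the sizing already treats drop-outs as lost to the analysis.

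**Step 2: analysed set under the named method.**
- Excluded: 0.20 × 92 = 18.4 survivors.
- Retained: 92 − 18.4 = 73.6, or 36.8 per arm.
- If a further 5% or 10% missed a single visit (assumed rates): 73.6 × 0.95 = 69.9 or 73.6 × 0.90 = 66.2 retained.

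Deletion is per person and per outcome. A missing caregiver scale does not remove the survivor's RNLI.

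**Step 3: power for 14 points with SD 21 (t-test).**
- 36 per arm: 0.797
- 36.8 per arm: 0.805
- 46 per arm, no loss: 0.886

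The 80% target is met at the planned loss.

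**Step 4: possible bias, as illustration only.** The following are assumptions that the article does not give: correlation 0.6 between visits; SD 21 at each visit; T2–T1 taken as 3 months minus baseline; 20% drop-out in each arm, all after month 3; and log-odds of drop-out changing by 1 per SD of the 3-month score wherever drop-out depends on outcome. The true effect is 14. Simulation with 200,000 per arm gives the between-group difference in change to 3 months:

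| Drop-out depends on the 3-month score | All participants | Completers |
|---|---|---|
| In neither arm | 13.9 | 14.0 |
| Alike in both arms | 14.0 | 14.0 |
| Control arm only (low scorers leave) | 13.9 | 12.5 |
| CTG arm only (low scorers leave) | 14.0 | 15.5 (15.4 in a repeat run) |
| Opposite directions (low scorers leave control, high scorers leave CTG) | 14.0 | 11.1 |

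With the directions reversed in the last row, a further run gave 16.8. In all these scenarios the 3-month scores exist, so an analysis using all available visits would keep them and avoid this distortion at 3 months.

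The SD of 21 plays two roles here. Step 3 takes it as the SD of the change score, as section 2.10 appears to. Step 4 takes it as the SD at each visit, which implies a change SD of 21 × √(2 × (1 − 0.6)) = 18.8. The bias figures should therefore not be combined with the power figures.

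**The case against.** **No contradiction is proven.** Intention-to-treat can be read narrowly, as analysis by assigned arm whatever the adherence. Imputation followed by the same ANOVA would satisfy even the wide reading. Missing-data handling is commonly left to an analysis plan, and that plan is not shown. This stands in part: a reader might infer that the primary result will certainly be a completer analysis, and the article does not support that certainty. It does not dispose of the point, because the article did not defer the choice. It states the test, the factors, the software, the sphericity check and the correction. Someone following that text alone would run a completer analysis and call it intention-to-treat.

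**Power is as planned.** This stands in full. A reader might infer that listwise deletion cuts power from 89% to 80%, but 89% assumes no loss at all, which the plan never claimed.

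**Large bias is not shown.** A harsher scenario is easy to build. If the lowest-scoring 30% of controls and a random 10% of the CTG arm miss month 6, the completer estimate is about 9.8 instead of 14. Nothing in the article supports so sharp a rule or a three-to-one imbalance, so that figure is close to a worst case and not an expectation. With the same rates but probabilistic drop-out, at log-odds of 0.5 or 1 per SD, the estimate is about 12.8 or 11.9.

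**The remedy is not unique.** A mixed model is one option and imputation is another. A mixed model also recovers little for people lost before month 3, who contribute only a baseline value. Both points stand.

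**Conclusion.** The point holds in conditional form. As written, section 2.11 pairs an intention-to-treat promise with a method that, unless missing values are imputed first, excludes every participant missing any visit on the outcome. At the planned 20% drop-out that is about 18 of 92 survivors in the RNLI analysis. The 20% is a planning assumption, and intermittent missed visits would add to the loss.

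The consequence is a completer population with possible bias. Its direction and size cannot be known in advance: under the moderate assumptions illustrated, it ranges from none to about 3 points either way on a 14-point effect. Because the bias is only possible, power is preserved, and an unseen analysis plan could add imputation, this is a should-fix matter.

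**What to change.** Make the primary analysis a likelihood-based mixed model for repeated measures (SPSS MIXED, REML) with group, visit and group-by-visit and an unstructured covariance. Use all available visits of all randomised participants in their assigned arm. The Mauchly and Greenhouse–Geisser step then falls away. Multiple imputation before the ANOVA is an acceptable alternative, provided it is stated. Either way, keep the complete-case ANOVA as a sensitivity analysis and settle the choice before outcome data are seen.

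The cost is a change of wording and slightly more analysis work in the software already named. The sample size need not change. The limits are that the model recovers little for participants lost before month 3, and that neither option removes bias if drop-out depends on unobserved values.

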**Methods:**

This single-blind (assessor), two-arm parallel superior randomised controlled trial will be conducted in the Hebei General Hospital, Shijiazhuang, China. Ninety-two participant dyads in home-based rehabilitation will be recruited and randomised to either CTG (intervention group) or a standard telerehabilitation group (control group). Participant dyads in the intervention group will follow a 6-step circle procedure and receive 12 teleoccupational coaching sessions over 3 months via WeChat. Data will be collected at baseline, after the intervention (3 months), and follow-up (6 months). The Reintegration to Normal Living Index will be the primary outcome to assess the participation of stroke survivors. Secondary outcomes will not only involve an observation of changes in activities of daily living, intrinsic motivation, motor function, and quality of life of stroke survivors but also will focus on the caregivers' perceived benefit and care burden. *Discussion*. This trial will assess the effects of CTG compared with standard telerehabilitation. We believe that the results of this study will add to the understanding of occupational therapy for stroke survivors in home-based rehabilitation and provide a reference for developing health policy and facilitating other chronic management. *Trial Registration Number*. The Chinese Clinical Trial Registry ChiCTR2200061107.

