### 2.4. Randomisation and Blinding

Participant dyads will be allocated to the CTG or the standard telerehabilitation group by using 1 : 1 randomisation sequences that are generated by IBM SPSS Statistics version 25. The random number sequence generation will be undertaken by a research assistant who is not involved in the assessment and intervention and will be placed in sequentially numbered, opaque, sealed envelopes for blinded group allocation.

Stroke survivors, primary caregivers, and occupational therapists will not be blinded due to the nature of the intervention. However, the assessor will be blinded to collect each outcome measure and undertake data entry. Furthermore, all participant dyads will meet with the same trained and blinded study assessor at all-time points to ensure consistency of outcome measures.

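### The trial is sized on one between-group RNLI difference, but the planned ANOVA names no deciding test, and its group main effect averages in baseline

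*Protocol article*

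**What the plan says.** The abstract names one primary outcome: "The Reintegration to Normal Living Index will be the primary outcome to assess the participation of stroke survivors". Section 2.10 bases the sample size on one comparison: "the minimum significant difference between the 2 groups in the T2–T1 interval for the RNLI in the survey is 14 points". For the spread it gives "The standard deviation of the measure was reported as 21 points in previous studies", without saying whether this is the SD of the score or of the change. It then sets alpha "at 0.05 (two-tailed) and the power at 80% and assuming a drop-out rate of 20%, the minimum sample size for each arm is 46".

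Section 2.11 specifies a repeated-measures ANOVA for the primary and secondary outcomes. Time has three levels (baseline, 3 months, 6 months) and treatment is the between-group factor. Of the effects it says: "We will evaluate the main effects of time, group, and time-group interaction effects". On the threshold it says: "The level of significance will be set at 0.05". It does not say which effect answers the primary question, and it lists no between-group contrast at a given time.

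The running text does not define T1 and T2. The timeline figure, which is not reproduced in the text at hand, may do so. Baseline to 3 months is the natural reading and is used below as an assumption.

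**The concern.** The sample size and the analysis address different quantities. The sample size concerns one difference over one interval. The analysis offers three F-tests, and none of them is that difference.

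- **Time** asks whether scores change over the visits with both arms combined. It is not a treatment comparison.
- **Group** compares the arms on the average of three visits. One of these is the randomised baseline, where the expected difference is zero, so the test cannot estimate the 14 points.
- **Group by time** is a 2-df test. It contains the sized contrast as one of its components, but a significant result does not show when the arms differ or which arm does better.

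Two of the three tests bear on treatment and neither has priority. The primary conclusion could therefore depend on a choice made after the results are known, and the estimate attached to it could be a diluted one.

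**Working it through.** **Inputs.** From section 2.10: difference 14, SD 21, two-sided 0.05, power 80%, drop-out 20%, 46 per arm. From section 2.4: allocation "by using 1 : 1 randomisation sequences". From section 2.11: three time levels including baseline. Assumed, because the article gives no figure: equal variance and equal correlation ρ across visits, with ρ from 0.3 to 0.8; and SD 21 read either as the SD of change or as the SD of the score.

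**1. The plan's own figure.** n = 2(1.96 + 0.84)² × 21²/14² = 35.3, so 36 per arm, and 36/0.8 = 45. By the exact t-test, 36 per arm gives 79.7% power and 37 gives 80.8%; 37/0.8 = 46.25. The stated 46 agrees with a two-group comparison of means.

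**2. What the group main effect estimates.** It is the mean of the between-group differences at the three visits, with 0 expected at baseline:
- 14 remains at 6 months: (0 + 14 + 14)/3 = 9.3
- 7 remains: (0 + 14 + 7)/3 = 7.0
- 0 remains: (0 + 14 + 0)/3 = 4.7

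This needs no assumption about correlation.

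**3. Power of the group main effect, 36 completers per arm.** The noncentrality is (n/2) × mean²/[σ²(1 + 2ρ)/3], on 1 and 70 df. If 21 is the SD of change, σ = 21/√(2(1 − ρ)); if it is the SD of the score, σ = 21. At ρ = 0.5 both readings give σ = 21 and a denominator of 441 × 2/3 = 294.
- Sustained effect, ρ = 0.5: 18 × 9.33²/294 = 5.33, power 63%
- Half remaining, ρ = 0.5: 18 × 7²/294 = 3.00, power 40%
- 3 months only, ρ = 0.5: 18 × 4.67²/294 = 1.33, power 21%

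For a sustained effect across the range of ρ:

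| SD 21 read as | ρ = 0.3 | ρ = 0.8 |
|---|---|---|
| SD of change | 85% | 24% |
| SD of score | 72% | 52% |

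**4. Power of the interaction, 36 completers per arm.** The noncentrality is (n/2) × Σ(d − mean d)²/[σ²(1 − ρ)], on 2 and 140 df. With SD 21 as the SD of change, σ²(1 − ρ) = 441/2 = 220.5 whatever ρ is.
- Sustained or 3 months only: sum of squares 130.67; 18 × 130.67/220.5 = 10.67, power 83%
- Half remaining: sum of squares 98; 18 × 98/220.5 = 8.00, power 71%

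The single 3-month change contrast has 79.7% on the same inputs.

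**5. Type I error if either treatment-related test counted.** Under the model the two tests are independent, so the rate is 1 − 0.95² = 0.0975.

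**The case against.** The strongest reply is that the interaction is the usual efficacy test in this design and that the sample size serves it well: 83% power for a sustained or 3-month-only effect, slightly above the 79.7% of the single contrast. That stands. A reader might infer that the stated 80% power belongs to none of the planned tests. The figures do not support this, because only the half-remaining case (71%) falls clearly below.

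Nor is the group main effect always the weaker test. Its estimate is diluted in every scenario considered, but at ρ = 0.3 with SD 21 as the SD of change its power for a sustained effect is 85%.

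A reader might also infer that the trial runs at a 9.75% error rate, or that it has three chances of success. The article states no rule by which either test wins, and the time effect is not a treatment test. The 9.75% is conditional on such a rule.

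A full analysis plan could name the deciding effect and add follow-up contrasts, and leaving that detail out of an article would not be a fault. But section 2.11 does fix the model, the inclusion of baseline as a level of time, the three effects and the threshold, and it gives no effect priority. That part is stated, not omitted.

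Section 2.12 calls the study exploratory, but does so to explain why there is no data monitoring committee. The abstract and section 2.1 describe a superiority trial, and section 2.10 gives a formal power calculation.

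**Conclusion.** The point holds as a mismatch between sizing and analysis. The sized quantity is one between-group difference over one interval; the analysis evaluates three effects at 0.05, none of which is that difference and none of which is named as decisive.

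The firmest part is the dilution of the group main effect, which rests only on randomisation and the inclusion of baseline. The power figures rest on the assumed correlation structure and on which SD the 21 points represent. The interaction's weakness is mainly one of interpretation. The error-rate figure applies only if success on either test were accepted.

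It would be wrong to conclude that 46 per arm is too few. That number reproduces, and it gives about 80% power for the sized contrast with 36 to 37 completers per arm if SD 21 is the SD of change. Reading T2–T1 as baseline to 3 months is an inference, but under another labelling it would still be a single-interval contrast that none of the three tests matches.

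**What to change.** - Define T1 and T2 in section 2.10, and say whether 21 is the SD of the change or of the score.
- In section 2.11, name one primary test: the CTG minus control difference in RNLI change over the sized interval (baseline to 3 months if that is what T2–T1 means), two-sided 0.05, reported with its 95% CI as a contrast from the longitudinal model.
- Make the 6-month difference secondary.
- State that the time effect, and the group main effect with baseline in the average, will not be used as evidence of efficacy.

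This changes wording only and should be settled before outcome data are seen. The sample size need not change if SD 21 is the SD of change. The cost is the loss of a second route to significance.

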### 2.12. Data Management

The medical data recording sheets, signed informed consent forms, and the data of the WeChat group (photos, videos) from participant dyads will be stored securely. The principal researcher ([name]) will be responsible for monitoring data in this study. Only authorised research assistants will have access to the trial data. In addition, as this study is an early, exploratory, short-term study without severe safety concerns, the Independent Data Monitoring Committee will not be set up.

### 2.14. Intervention Fidelity

The occupational therapist will document the content of the coaching home-based rehabilitation by taking notes and session video recordings to monitor intervention fidelity. The principal researcher will test fidelity by rating 3 randomly selected video recordings of sessions per participant.

### 2.15. Dealing with Contingencies

The first possible contingency in the study is the difficulty in recruiting an adequate number of stroke survivors to meet the sample-size requirement. If necessary, expanding the scope of recruitment to the departments of neurology, neurosurgery, or other hospitals in Shijiazhuang should be considered. The second possible unexpected problem is the high drop-out rate of participants. To prevent this possibility, researchers will improve patients' correct perception of clinical trials and establish appropriate expectations. In addition, if the participants feel uncomfortable during the intervention period, researchers will pause the intervention or provide them with appropriate treatment.

## 3. Discussion

Coaching, which emerged from motivational interviewing, is the practice of health education and health promotion within a coaching context to enhance the well-being of individuals and facilitate the achievement of their health-related goals [28, 29]. Motivational interviewing, a core component of coaching strategies, focuses on motivating the patient to achieve goals that enhance the quality of life and improve the outcome of rehabilitation [28]. In our study, motivational interviewing methods will be adopted for stroke survivors and caregivers, such as emotional support, expressing empathy, supporting self-efficacy, looking forward, looking back, and so on. These strategies will equip them with knowledge and motivation to change behaviours or to identify advantages and barriers for participant dyads to achieve goals in the current situation [30, 31]. Furthermore, coaching sessions are crucial to ensure positive health outcomes, which can help the occupational therapist find and solve timely problems that happen to patients and their caregivers. Coaching sessions will be carried out by structured procedures, including open-ended questions, reflective listening, affirmation, guiding, and summary, which are easier to conduct for occupational therapists who, by their vocation, are nonprofessional coaches [32]. Most importantly, this process will enable the participant dyads to learn to independently solve relevant problems in future home-based rehabilitation.

Many fundamental coaching principles are congruent with occupational therapy values and commitment to client-centred practice [33]. In our study, the occupational therapist will use the COPM model, which is widely used in stroke rehabilitation research, to help participants identify goals. Goal setting should be individualised and realistic to motivate participants to achieve their goals. However, some previous home-based rehabilitation programs paid more attention to physical functions but ignored the demands, and psychological and social functions of stroke survivors, which could not bring a long-term effect [34]. In contrast, researchers focus on the demands of patients and make activities of daily living integrate into occupational plans so that they can quickly return to home life and maintain a long-term effect. According to recent reports, approximately 80% of stroke survivors only participate in a few meaningful activities, which decreases their quality of life and increases the caregivers' burden to different degrees [35]. Participation is the ability to engage in meaningful activities, which is considered a significant outcome measure, especially for home-based stroke survivors [36]. Therefore, enhancing the participation of stroke survivors is prioritised by occupational therapists. Furthermore, researchers choose the RNLI as the primary outcome in this study because it has advantages in assessing overall participation of stroke from the perspective of daily functioning and perception of self and considering the person's satisfaction with the present situation, which is the best fit with the purposes of our study. However, there is relatively little research about participation in stroke. It is anticipated that the results of this intervention will provide related evidence to inform peers in home-based rehabilitation.

In addition, caregivers play an important role in home-based rehabilitation, which are not only in charge of taking care of stroke patients and assisting and monitoring patients participating in rehabilitation training but also bear substantial mental pressure and psychological burden [37, 38]. In this study, we focus on the role and burden of caregivers and listen to their demands. Moreover, the occupational therapist will provide emotional support and stroke-related knowledge for caregivers by CTG in order to improve quality of life and decrease burdens. In terms of perceived benefits, CBFS is chosen to measure this outcome, which takes individual growth, health promotion, family growth, and self-sublimation into consideration and supports caregivers to realize their growth and find personal meaning during the caregiving experience.

Occupational plans for stroke survivors are crucial to enable them to gain well-being. However, making occupational plans is challenging for occupational therapists. Therefore, we combined the PEO model with the SMART principle to optimise both. First, the PEO model will guide occupational therapists to analyse residual function, support available, and degree of challenge and clear the key points of plans from different aspects of the person, the environment, and the demands of the occupation [39]. Second, it is a complex but essential requirement for researchers to set plans. Some of the characteristics of programmes that effectively alter behaviours should be considered. The SMART principle will satisfy this requirement and play a vital role in structuring and quantifying plans to ensure that participants achieve their goals [40].

The delivery of an intervention needs to be safe, private, and easy to use. WeChat is a free software created by the Tencent Technology Company to provide instant messaging services for clients, which supports the quick sending of free voice messages, videos, and pictures as well as voice and video calls. The app is highly popular in China and has the advantages of easy operability in real-time while being convenient, fast, and economical. In the home-based rehabilitation period, stroke survivors may experience various confusing problems. Therefore, timely communication is essential for both occupational therapists and participants. At least 5 videos each week, video call sessions once a week, and needs-based WeChat contact will allow occupational therapists and participants to solve problems or adjust plans without delay.

Several vital steps affect study fidelity. First, researchers have developed standardised and logical intervention procedures based on coaching theory, occupational therapy strategies, and behavioural change techniques. Second, training interveners and documenting the content of the intervention will improve adherence to the study design. Third, stroke survivors will be asked to send pictures and videos regularly to monitor the completion of the plan mutually. In addition, we will offer a questionnaire survey to participants to assess their general satisfaction across various aspects of the intervention and collect data on the number of participants who drop out of the study to analyse reasons for quitting.

The protocol has some limitations. First, because of the nature of the intervention, it is impossible to blind the occupational therapists and participants. Moreover, emotional support is a crucial aspect of CTG. However, occupational therapists have to provide this support due to professional ethics when stroke survivors in the control group ask for help. Therefore, both possibilities may increase the risk of bias. Second, successful home-based rehabilitation is a sustainable long-term process whereas our observation period is for 6 months. It is expected that we can explore the efficacy of a longer duration of the intervention and follow-up. Finally, future studies should take economic effects into account.

